### Participants

Adults 65 years and older who are admitted to an internal medicine acute care ward with an expected length of stay of more than 2 days, who are high-cost users defined as at least one other hospitalization within the previous year, who are taking five or more chronic medications including at least one high risk medication, and provide informed consent. Patients will be excluded if they are being discharged to long-term care or other setting where they or their caregiver is not in charge of their medications. It is estimated that at least *10 patients daily* meet these eligibility criteria.

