**Fig. 2 Fig2:**
[figure not shown]
IMPROVE-IT HRM clinical approach

While the patient is still hospitalized, the high-risk medications care plan begins, and the team ensures close communication with the primary team, coordinates a detailed discharge medication reconciliation (documenting medication changes with rationale, formulating an accurate discharge prescription including rapid access to new medications), ensures circle-of-care communication, and sees the patient via virtual visit twice in follow-up at 1 week and 1 month after hospital discharge to complete and consolidate the care plan. Since this is a pragmatic trial, concomitant care is not prohibited. Pre-testing of the intervention with several patients has shown that the initial consult and two follow-up visits can be completed in less than 1 h each.

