**A. Feasibility outcomes**					
A1. Primary feasibility outcomes	A1.1 Participant recruitment rates	≥ 30% of those eligible will be considered success	Percentage recruited and rate of recruitment (of those screened, of those eligible, and of those approached)	Counts (%) over time	Baseline
	A1.2 Participant retention rate	≥ 90% is considered success	Percentage of those recruited who complete at least end-study outcome	Counts (%) end study	End of study
	A1.3 Intervention adherence	≥ 90% is considered success	Percentage of those recruited who completed each phase of the study (baseline, virtual visits, end of study outcomes)	Counts (%) over time	End of study
	A1.4 Study resource utilization	< US $1500 per patient recruited and completing the study	Study costs per patient recruited to end follow-up	Cost of personnel, supplies, travel, etc. to run the study	End of study
A2. Secondary feasibility outcomes	A2.1 Clinical Pharmacology & Toxicology (CPT) Recommendation Acceptance — Primary Team	> 50% medication recommendations	% CPT recommendations per patient accepted (continued or implemented)	Counts (%) after consult	Hospital discharge
	A2.2 CPT recommendation acceptance — patients	> 50% medication recommendations	% CPT recommendations per patient that were initially followed by patient	Counts (%) after consult	Hospital discharge
	A2.3 CPT recommendation adherence — Patients	≥ 90% is considered success	% CPT recommendations per patient still being followed at end of study	Counts (%)	End of study
	A2.4 CPT consultation volume capacity	Number of eligible patients available to approach is > 3 per day	Volume of eligible patients available to approach per week	Counts	Baseline
	A2.5 Potential to intervene entirely virtually	> 90% patients can be managed through follow-up entirely by virtual care platform	Number (%) patients entering follow-up who do not require an unscheduled in-person visit Number of follow-up visits conducted using secure videoconference platform	Counts (%)	End of study
**B. Clinical outcomes**		**Hypothesis**			
B1. Primary clinical outcomes	B1.1 Drug therapy problems improved	Intervention group will have more improved drug therapy problems compared to control group (e.g., dose adjusted, discontinued, interacting drugs removed)	Percentage of baseline drug therapy problems identified by APEQ that have been improved by end of study	Mean difference in APEQ score changes	End of study

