#### Secondary outcomes

The *secondary feasibility outcomes* of CPT consultation include recommendation acceptance and adherence by primary team and by patients, consult volume capacity, and potential to apply the intervention entirely through virtual visits including eConsults. Thresholds for success are described in Table 2.*The secondary clinical/patient-important outcomes* will include the following:Adverse drug events (ADEs) defined as “Harm caused by exposure to a drug” adjudicated using Leape and Bates scale (6 - definitely due to medication, 5 - probably due to medication, 4 - possibly due to medication, 3 - possibly due to disease, 2 - probably due to disease, 1 - definitely due to disease, 5 and 6 considered ADE) [74]. ADE preventability will be evaluated using the recommended “best practice”-based definition [70].Medication errors defined as an error (of commission or omission) at any step along the pathway that begins with prescribing and ends with the patient taking the medication [74]. We will use the standard NCC-MERP classification system [71, 75].Number of medications per patient end study compared to baseline.Patient problems with medications: The COMPETE Medication Problems Questionnaire measures problems with medication access, handling, beliefs, and adherence [76].Medication knowledge assessment: This will be assessed using the Medication Knowledge Assessment form, which tests knowledge of medication name, indication, dosage instructions, and precautions [77].Coordination and continuity of care: Adapted from Health Quality Ontario’s draft guidance and a Rand instrument, the Coordination and Continuity of Care Questionnaire is designed to measure the quality of the transitional and follow-up care. We will focus on medication reconciliations and education and circle-of-care communications [78, 79].Patient quality of life: We will use the general EQ-5D-5L, a five-level measure of health status and utilities well validated in Canada and based on self-reported mobility, self-care, usual activities, pain discomfort, and anxiety/depression [80–82]. We will also use a “condition-specific” QOL measure, the medication-related quality-of-life measure which is designed for people living with polypharmacy [83].Satisfaction with care: Satisfaction reported by patients and by key health professionals is one of the recommended outcomes to report in medical research, as it may influence adherence [84, 85]. This outcome will be assessed by the Patient/Caregiver Study Satisfaction Survey and by the Provider Study Satisfaction Survey [86].Health resource utilization: This is a key outcome to determine cost-effectiveness and cost-utility which then determines whether healthcare systems might pay for this type of care [87, 88]. Using questionnaire and chart review, we will capture emergency department visits, hospitalizations, unplanned physician visits, and medication costs, including out-of-pocket medication costs in follow-up [79, 88].

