#### Impact of research

By creating a network of clinicians, patients, researchers, drug policy advisors, information technology advisors, quality improvement advisors, and hospital and national medication safety administration, we hope to strengthen and broaden the usual dissemination of research to practice We expect the pilot study to inform a future definitive trial by identifying solutions to overcome potential limitations including the following:The CPT team is a scarce resource which limits eventual generalizability. Based on pilot results, we will plan to study how physician assistants and clinical pharmacists can be trained to do this work.The short follow-up of 3 months is typical of transitional care initiatives but may be too short to show impact on clinical outcomes.The single-center design aids feasibility of the pilot but limits generalizability. A larger trial, if feasible, will aim to recruit other hospitals using the Epic EMR or members of the national deprescribing network.A definitive trial will highlight clinical outcomes as primary outcomes.

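### Secondary feasibility outcome A2.4 is labelled CPT consultation capacity but counts patients available before randomization, so it does not test whether the CPT team can deliver the consults

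*Protocol article*

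**What the plan says.** Table 2 of the protocol article lists "A2.4 CPT consultation volume capacity" among the secondary feasibility outcomes. Its success criterion is "Number of eligible patients available to approach is > 3 per day", its measure is "Volume of eligible patients available to approach per week", its analysis is counts, and it is assessed at baseline. The Secondary outcomes section places it among the feasibility outcomes of CPT consultation, as "consult volume capacity, and potential to apply the intervention entirely through virtual visits including eConsults", and refers to Table 2 for the thresholds.

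Four other statements bear on it:

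- Participants gives the expected supply: "It is estimated that at least *10 patients daily* meet these eligibility criteria".
- Intervention says that allocation to the intervention arm is what triggers the CPT consult request. From pre-testing it reports that "the initial consult and two follow-up visits can be completed in less than 1 h each".
- Impact of research lists, among the limitations that the pilot should help to overcome: "The CPT team is a scarce resource which limits eventual generalizability".
- The detailed research question asks whether it is feasible for an expert clinical pharmacology team to coordinate and improve medication management across the transition out of hospital, so as to justify a large trial.

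**The concern.** The label and the Secondary outcomes text present A2.4 as a test of how many consults the CPT team can handle. The criterion and the measure count something else, namely how many patients the wards supply. Supply and delivery can come apart. Many patients may be available while the team sees few of them in time, and eligibility requires an expected stay of only more than 2 days. A reader of the pilot report who sees that consultation capacity met its criterion would naturally conclude that the team can cope with the workload, and the number would not support that conclusion. Since the research question concerns what this team can deliver, and the article itself calls the team scarce, the one outcome named for capacity ought to depend on the team's activity.

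**Working it through.** **1. Can CPT activity change A2.4?** The order of events in Recruitment and randomization and in Intervention is: eligibility confirmed, medication history completed, eligibility cleared with the primary team, approach, consent, baseline assessment, randomization, CPT consult requested. A2.4 is counted at the approach step. The consult comes at the end. With 30 intervention patients, 0 of 30 or 30 of 30 completed consults give the same A2.4 value.

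**2. Does another outcome cover delivery of the inpatient consult?**

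| Outcome | What it counts | Shows a missed inpatient consult? |
|---|---|---|
| A1.3 | Completion of each phase; baseline, virtual visits and end-of-study outcomes are listed | Follow-up visits yes; inpatient consult not listed |
| A1.4 | Study cost per patient | No |
| A2.1 to A2.3 | Share of CPT recommendations accepted or still followed | No; a patient without a consult has no recommendations to count |
| A2.5 | Follow-up managed virtually | No |

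Table 3 schedules the consult during the inpatient stay, but no outcome is attached to its completion.

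**3. How demanding is the threshold?** The article gives no derivation for 3 per day, so there is no figure to reproduce. Set against the estimate in Participants:

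- Ratio: 10 / 3 = 3.3.
- Share of the estimated 10 that must be available to exceed the threshold: 3 / 10 = 30%. At 40% the count is 4 per day (passes), at 30% it is 3 per day (does not exceed 3), at 20% it is 2 per day (fails).
- If the criterion is read day by day with Poisson counts (an assumption), the probability of more than 3 is 1 − e^(−m)(1 + m + m²/2 + m³/6), where m is the mean available per day:

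| Share available | m | P(more than 3) |
|---|---|---|
| 100% | 10 | 0.990 |
| 50% | 5 | 0.73 |
| 30% | 3 | 0.35 |

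- If the 10 are patients present on the wards and A2.4 means newly available patients (the article states neither), an assumed stay of 5 to 7 days gives 10 / 5 = 2.0 to 10 / 7 = 1.4 new patients per day, below the threshold.

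**4. Units.** The criterion is per day and the measure per week. More than 3 per day is more than 15 per week on 5 recruiting days, or more than 21 on 7. The article does not say which applies.

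**5. The load that A2.4 leaves out.** Three contacts of at most 1 h make at most 3 CPT hours per intervention patient, so at most 30 × 3 = 90 h in the whole pilot. At 10 eligible per day and the 30% recruitment target, 3 patients per day are recruited and 1.5 allocated to the intervention, which is at most 1.5 × 3 = 4.5 CPT hours per day. A2.4 compares no such figure with the hours the team has.

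**The case against.** The strongest defence is that the label may mean the site's potential consult volume. On that reading the measure fits its name, and checking an advance estimate of patient numbers is a proper task for a pilot. A threshold below the planning estimate is not in itself a defect. This stands as an argument for keeping the count. It does not save its use as evidence of the team's capacity, because delivery stays untested on either reading.

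A reader might infer three stronger things that the article does not support:

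- *That the criterion is already met, or can hardly fail.* This equates patients who "meet these eligibility criteria" with the narrower group available to approach, who have also passed the medication history and the clearance by the primary team. The 0.990 above holds only if all 10 are available.
- *That non-delivery would go unseen altogether.* A1.3, listed in Table 2 as a primary feasibility outcome with a 90% threshold, would show a failure to complete the virtual visits. The gap is the inpatient consult and the team's workload.
- *That the article calls CPT scarcity its main limitation.* It is one of four listed, and it is framed as a limit on generalizability.

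Nor do the 90 hours demonstrate a bottleneck. They are a small total, and the pre-testing result suggests that each contact is manageable. The difference between day and week is a matter of conversion once the number of recruiting days is stated.

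**Conclusion.** The point holds as a mismatch between what A2.4 is called and what it measures. As written, consultation capacity would be judged adequate on patient supply alone, and nothing the CPT team does could change the result. This rests only on the wording of Table 2 and the order of steps in the article, not on any numerical assumption.

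That the threshold is lenient is conditional. It is easy if most of the estimated 10 or more patients per day can be approached, and it can fail if about 30% or fewer can, or if the estimate refers to patients present rather than new ones. The consequence is modest: A2.4 is a secondary, descriptive feasibility count and affects neither the sample size, nor the primary criteria, nor the comparison between arms. It is still worth correcting, because it is the one outcome named for capacity in a pilot that asks what this team can deliver.

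**What to change.** 1. Keep the present count, rename it eligible patient volume, and state criterion and measure in the same unit, with the number of recruiting days per week. Say whether it counts patients present or newly available.
2. Define A2.4 as the percentage of intervention patients whose initial CPT consult was completed before hospital discharge, with all patients allocated to the intervention as denominator. The team should set the threshold before looking at the data. With 30 patients, each one moves the percentage by 1 / 30 = 3.3 points, so it helps to write the threshold as a count as well.
3. Report CPT clinician time per patient descriptively, for planning the larger trial.
4. Do not use consults per consultant per week as the criterion. In a 30-patient arm that figure is capped by the rate of randomization, so it would reflect recruitment pace rather than capacity.

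The cost is a wording change in Table 2 and a small query on consults already recorded in the EMR template, with no added patient contact. If clinician time is not already logged there, it would need a short entry per contact. The downside is that the new criterion may be harder to meet than the present one.

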	**Outcome**
Feasibility	1. Participant recruitment rates
	2. Participant retention rate
	3. Trial resource utilization, costs
	4. Recommendation acceptance rates by primary team
	5. Recommendation acceptance rates by patient
	6. Recommendation adherence rates by patient
	7. CPT consultation volume capacity
	8. Potential to intervene entirely virtually (online)
Clinical	**1.** Medication management outcomes a) # inappropriate medications, # drug therapy problems improved, # high-risk medication problems improved, all measured by APEQ b) # medications per patient end study versus baseline
	**2.** Adverse drug events including adverse drug withdrawal event
	**3.** Medication errors, including preventability
	**4.** Patient problems with medications questionnaire (includes general adherence)
	**5.** Patient knowledge of medications
	**6.** Coordination and continuity of care
	**7.** Patient quality of life (EQ-5D-5L and medication-related QOL)
	**8.** Satisfaction with care (patients and providers)
	**9.** Health resource utilization, including clinical events of death, ED visits, hospitalizations, physician visits, other providers including diagnostics utilization, medication costs

**Table 2 Tab2:** IMPROVE-IT HRM study outcomes and measures

	Outcomes	Criteria for success	Outcome measure	Method of analysis	When assessed

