### Follow-up

Patients will be followed until 3-month posthospital discharge or until death or admission to long-term care home, whichever occurs first. Follow-up visits will be conducted by videoconference via Epic EMR or Ontario Telehealth Network, or by phone call, depending on the patient’s digital technology capability.

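### Table 2, A2.5: the > 90% virtual-care criterion is scored by the absence of an unscheduled in-person visit, so missed remote visits cannot lower it and it can be met with no video visit

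*Protocol article*

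**What the plan says.** Table 2 of the protocol article, row A2.5, sets its success criterion as "> 90% patients can be managed through follow-up entirely by virtual care platform". The measure cell beside it holds two items:

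- "Number (%) patients entering follow-up who do not require an unscheduled in-person visit"
- "Number of follow-up visits conducted using secure videoconference platform"

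The method cell for the row is a count with a percentage, and assessment is at end of study. Table 1 lists the same outcome as feasibility item 8, "Potential to intervene entirely virtually (online" (the bracket closes after the last word). The Secondary outcomes section describes it more broadly, as delivery through virtual visits with eConsults included, and refers to Table 2 for the thresholds.

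On delivery, the Intervention section says the team "sees the patient via virtual visit twice in follow-up at 1 week and 1 month after hospital discharge". The Follow-up section adds that "Follow-up visits will be conducted by videoconference via Epic EMR or Ontario Telehealth Network, or by phone call", with the choice resting on what technology the patient can use.

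Completion of visits appears in another row, A1.3, with a threshold of at least 90%: "Percentage of those recruited who completed each phase of the study (baseline, virtual visits, end of study outcomes".

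**The concern.** The criterion asks whether patients were managed remotely from start to finish. The percentage that can be set against it asks only whether an unplanned face-to-face visit was avoided. A patient can avoid one because remote care worked, or because no care took place. The measure does not separate the two, and nothing in it requires a remote visit to have happened.

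The videoconference count could show how much of the follow-up ran on the platform, but it is a visit-level figure with no threshold and no stated part in the pass or fail decision.

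The discussion in the abstract rests the potential for wide benefit on offering a scarce specialty through virtual care. A2.5 is the only row of Table 2 that sets a threshold for that mode of delivery. A pass that missed visits cannot prevent is weak support for the conclusion.

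**Working it through.** The > 90% figure is a chosen cut-off, so there is no power or sample-size calculation to reproduce. The check is what the cut-off requires and which patient mixes satisfy it.

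**Inputs.** 30 patients per group (Sample size); two scheduled follow-up visits per intervention patient, at 1 week and 1 month (Intervention); success above 90% (Table 2, A2.5). I assume that all 30 intervention patients enter follow-up. The patient mixes are invented for illustration, and each patient completes either both scheduled visits or neither.

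**Step 1: the cut-off as a count.** 27/30 = 90.0%, which is not above 90%. 28/30 = 93.3%, which is. So 28 successes are needed.

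**Step 2: three ways to score.** Let v = managed by video only, p = by phone only, m = entered follow-up but completed no visit, u = needed an unscheduled in-person visit, and n = v + p + m + u = 30.

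- As written: (v + p + m)/n
- Managed remotely, phone accepted: (v + p)/n
- Managed by video only: v/n
- Visits by video: 2v of 2n = 60

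| Mix | v | p | m | u | As written | Remote, phone accepted | Video only | Video visits |
|---|---|---|---|---|---|---|---|---|
| a | 0 | 28 | 0 | 2 | 93.3% pass | 93.3% pass | 0% | 0 of 60 |
| b | 0 | 24 | 4 | 2 | 93.3% pass | 80.0% fail | 0% | 0 of 60 |
| c | 15 | 10 | 3 | 2 | 93.3% pass | 83.3% fail | 50.0% | 30 of 60 |
| d | 24 | 3 | 1 | 2 | 93.3% pass | 90.0% fail | 80.0% | 48 of 60 |
| e | 28 | 0 | 0 | 2 | 93.3% pass | 93.3% pass | 93.3% | 56 of 60 |

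The measure as written gives the same result in all five. It depends only on u, since (v + p + m)/n = 1 − u/n, and 1 − 2/30 = 93.3%. Moving a patient from v or p to m leaves it unchanged.

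**Step 3: does A1.3 close the gap?** Apply A1.3's threshold of at least 90% to the virtual-visit phase in the 30 intervention patients, and assume that the 2 in-person patients also completed their scheduled visits. Mix b gives 26/30 = 86.7%, so A1.3 fails and the missed visits show there. Mix c gives 27/30 = 90.0% and mix d gives 29/30 = 96.7%, so A1.3 passes. In c and d both rows pass, while the share managed remotely is 83.3% and 90.0%, neither above 90%.

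**The case against.** The strongest reply is that virtual is not confined to video in this protocol. The 1-week and 1-month contacts are called virtual visits, the Follow-up section allows them "or by phone call, depending on the patient’s digital technology capability", and the Secondary outcomes section extends the outcome to eConsults. A reader might infer from mix a that counting phone-only patients as successes is itself an error. The document does not support that. Only *online* in Table 1 and *platform* in Table 2 point to video, and neither is defined. If phone is meant to count, mix a is a true pass. What stands is that the terms do not agree with the phone option, and the row does not say which governs.

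A reader might also infer that patients never seen at all are scored as successes. That goes too far. The denominator is patients entering follow-up, a term the article leaves undefined, and someone who never starts may fall outside it. The criterion's own words would also not describe a patient without contact as managed. What stands is narrower: a patient who enters and then completes no visit is a success on the only percentage that can be compared with 90%.

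A1.3 does set its own threshold for completing virtual visits, so missed visits are not hidden. It is a separate criterion, however, and as Step 3 shows both can pass while the share managed remotely falls short.

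The method cell's percentage could apply to the videoconference count, and two planned visits per patient give a natural denominator. Low video use would then be reported in the same row. It still would not affect success, because no threshold is attached.

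Finally, a condensed article may leave definitions to a fuller protocol. That excuses the undefined terms, but not a criterion and a measure that are printed side by side and do not match.

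**Conclusion.** The point holds as a mismatch between the A2.5 criterion and its patient-level measure. Missed visits cannot lower the score, and the threshold can be met with 0 of 60 follow-up visits by video. The first defect does not depend on how phone is classed: with phone accepted, the row can read 93.3% when 80.0% to 90.0% of patients were managed remotely (mixes b to d). The second matters only if the sponsor means the outcome to be about video.

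These sizes rest on the assumed 30 patients entering follow-up and on invented mixes. They show what the measure permits and do not predict what will happen. The documents do not support saying that phone follow-up is non-virtual or that a video-only definition is required.

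A2.5 is a secondary outcome with descriptive analysis. The primary feasibility outcomes and the clinical comparison are untouched; the effect is limited to what the pilot may conclude about virtual delivery.

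**What to change.** Reword row A2.5 as follows.

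- **Denominator:** intervention-arm patients entering follow-up, with that term defined. Patients whose follow-up ended by death or long-term care admission before the visits were due should not count as failures, since the Follow-up section ends their follow-up at that point.
- **Numerator:** both scheduled follow-up visits completed remotely, and no unscheduled in-person visit.
- **Threshold:** apply > 90% to this proportion.
- **Mode:** report the video and phone shares of completed visits separately.
- **Terms:** state whether phone counts as virtual, and bring the Table 1 label and the Table 2 criterion into line with the phone option. If phone does not count, restrict the numerator to video.

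The cost is one table row and the matching label in Table 1. Video visits are already to be counted under the second measure and visit completion under A1.3, so little or no new data collection is needed. The reported figure may be lower than under the present measure.

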### Design

This is a single-center pragmatic pilot randomized trial (RCT) with 1:1 patient-level concealed-allocation randomization with blinded outcome assessment and data analysis [38]. Randomization provides the highest quality methods to minimize bias, the pragmatic design ensures relevance to clinical practice essential for implementation, and a pilot RCT addresses feasibility of a large definitive subsequent RCT directly without waste of research dollars [39, 40]. A study flow diagram is shown below in Fig. 1. Study setting is a 700-bed academic hospital with a busy urgent care and emergency department providing medical, surgical, psychiatric, and obstetric-gynecology inpatient and outpatient care in Hamilton, Ontario.

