B2. Secondary clinical outcomes	B2.1 Adverse drug events	Intervention will have lower event rates	Event rate counts from end of study interviews using Leape and Bates scale	Counts (%)	End of study
	B2.2 Medication errors	Intervention will have fever medication errors	NCC-MERP definition	Counts (%)	End of study
	B2.3 Number of medications	Intervention will have more medications deprescribed per patient	Number of medications end study compared to baseline	Counts	End of study
	B2.4 Patient problems with medications	Intervention will have fewer medication problems, including better adherence	COMPETE Medication Problems Questionnaire	Difference in mean group scores	End of study
	B2.5 Medication knowledge - patient	Intervention will have higher scores	Medication knowledge assessment form	Difference in mean group scores	Baseline and Eed of study
	B2.6 Coordination and continuity of care	Intervention will have higher ratings	Coordination and Continuity of Care Questionnaire	Difference in mean group scores	End of study
	B2.7 Patient quality of life	Intervention will improve more	EQ5D-5L and MedQOL	Difference in mean group change scores	End of study
	B2.8 Patient satisfaction with care	Intervention will have higher scores	Patient Satisfaction Questionnaire	Descriptive analysis	End of study
	B2.9 Provider satisfaction with care	Intervention will have higher scores	Physician, pharmacist Study Satisfaction Questionnaire	Descriptive analysis	End of study
	B2.10 Cost-effectiveness/ health resource utilization	Intervention will be cost-effective using a threshold of US $50,000 per QALY	Cost per adverse drug events avoided and incremental cost per quality-adjusted life-years (QALYs) using EQ5D-5L utilities	Economic analysis	End of study

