#### Primary outcomes

There are two types of primary outcomes that will be evaluated:The *primary feasibility outcomes* will be recruitment and retention rate for eligible patients and the estimated resources required per patient to complete the main trial (program delivery costs). We aim for at least 30% recruitment of those eligible, 90% retention of those recruited, and no more than US $1500 per patient spent on running the pilot trial. This figure is based on the limits of peer-reviewed RCT funding for a full trial.The *primary clinical outcome* will be the number of drug therapy problems remediated including the number of high-risk medications improved (for example, dose adjustment, discontinued, seriously interacting drugs removed) at 3-month posthospital discharge end-study visit, as judged by adjudicators using APEQ.

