### Sample size

Since this is a pilot RCT, we will aim for 30 patients per group or 60 in total as this number is likely to provide adequate evidence regarding feasibility for ramp-up to a definitive trial.

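### Table 2 names unadjusted change-score or mean-score comparisons for outcomes with a pre-randomization baseline; baseline-adjusted analysis would be more precise, once the B1.1 measure is settled

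*Protocol article*

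**What the plan says.** Table 2 of the protocol article has a column for the method of analysis.

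- **B1.1, drug therapy problems (primary clinical outcome):** the method is "Mean difference in APEQ score changes". The measure in the same row is "Percentage of baseline drug therapy problems identified by APEQ that have been improved by end of study". The Primary outcomes section instead describes the "number of drug therapy problems remediated including the number of high-risk medications improved".
- **B2.7, EQ-5D-5L and MedQOL:** "Difference in mean group change scores".
- **B2.5, medication knowledge:** "Difference in mean group scores". The timing column lists both baseline and end of study, but the row does not say how the baseline score enters.

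Table 3 schedules APEQ, EQ-5D-5L, MedQOL and the medication knowledge assessment at baseline and 3 months in both groups. Recruitment and randomization places allocation after the baseline assessments, so the baseline values are valid covariates. Statistical analyses names no regression model or baseline adjustment. The closing paragraphs of Secondary outcomes list potential predictors of outcome, but commit only to examining how complete those data are.

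On size, the plan says "we will aim for 30 patients per group or 60 in total".

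**The concern.** When an outcome is measured before and after randomization, there are three usual comparisons: the end score, the change from baseline, and the end score adjusted for baseline (ANCOVA). The change score subtracts the whole baseline value, which over-corrects when the two measurements correlate less than perfectly. The end score makes no correction. Each therefore has more variance than ANCOVA, and each shifts with whatever baseline difference chance produces, in opposite directions.

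In a trial of 60 patients such differences are common. B1.1 adds a structural reason: a patient can have only as many problems improved as were present at the start, so a count of improvements depends on the starting count.

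At stake is the width of the intervals around the clinical estimates. The Abstract makes a definitive trial conditional partly on promising clinical outcomes, so these estimates have a use even in a pilot.

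**Working it through.** **The plan's own figure.** 30 + 30 = 60. No power, significance level, effect size or SD is given for any clinical outcome, so nothing more can be reproduced.

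**Inputs.** Allocation is 1:1 with 30 per arm. The retention target in Table 2 is at least 90%, and 30 × 0.90 = 27 completers per arm. The documents give no correlation r between baseline and 3 months. I assume 0.3, 0.5 and 0.7, with equal SDs at the two times.

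**Precision.** In units of the single-score variance, the variance is 1 for the end score, 2(1 − r) for change and 1 − r² for ANCOVA. ANCOVA relative to change is (1 − r²) / [2(1 − r)] = (1 + r)/2.

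| r | Change | End score | ANCOVA | ANCOVA ÷ change | ANCOVA ÷ end score |
|---|---|---|---|---|---|
| 0.3 | 1.40 | 1.00 | 0.91 | 0.65 | 0.91 |
| 0.5 | 1.00 | 1.00 | 0.75 | 0.75 | 0.75 |
| 0.7 | 0.60 | 1.00 | 0.51 | 0.85 | 0.51 |

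So ANCOVA has 35%, 25% and 15% less variance than change, and 9%, 25% and 51% less than the end score. At r = 0.5, 27 patients per arm carry the information of 27 / 0.75 = 36.

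Estimating the slope multiplies the ANCOVA variance by 1 + 1/(2n − 4), which is 1.02 at n = 27. The ratios become 0.66, 0.77 and 0.87 against change, and 0.93, 0.77 and 0.52 against the end score. With this factor included, ANCOVA was still the most precise of the three at every r tried from 0.2 to 0.8. A simulation with 30 per arm and 20,000 runs gave matching standard errors:

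| r | Change | End score | ANCOVA |
|---|---|---|---|
| 0.3 | 0.305 | 0.259 | 0.249 |
| 0.5 | 0.260 | 0.257 | 0.227 |
| 0.7 | 0.199 | 0.258 | 0.186 |

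(SD units.)

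**Chance imbalance.** The SD of the baseline difference between arms is √(2/n), which is 0.258 SD at 30 per arm and 0.272 SD at 27. A difference larger than 0.25 SD in either direction is expected in about 33% of trials (36% at 27 per arm). A baseline difference D shifts the change-score estimate by −(1 − r)D and the end-score estimate by rD. At D = 0.25 SD and r = 0.3, 0.5 and 0.7, the shifts are −0.175, −0.125 and −0.075 SD for change, and +0.075, +0.125 and +0.175 SD for the end score. ANCOVA shifts by about 0.

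**B1.1.** The effect of adjustment depends on which measure is meant, so it was simulated for each. The inputs were 27 per arm, a mean of 2.8 baseline problems and 16.6% improved in controls. Both figures are for potentially inappropriate medications in the chart review under Priority situations, used here as proxies. Further assumptions were 50% or 16.6% improved with the intervention, Poisson or twice-Poisson variance of the baseline count, and 0 or 0.5 new problems per patient.

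- **Number improved or change in count:** adjusting for baseline count gave variance ratios of about 0.53 to 0.80 with the assumed effect and about 0.72 to 0.95 with none.
- **Percentage of baseline problems improved:** adjusting for baseline count gave 1.02 to 1.03, with or without an effect. There is no gain and a trivial loss.

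**The case against.** **The percentage measure already accounts for baseline.** This stands. The percentage is scaled to each patient's starting count, and the simulation shows no gain from adjusting it. The precision argument for B1.1 therefore applies to the score change named as its analysis and to the number in Primary outcomes, but not to the percentage. Neither the percentage nor the number improved has a baseline value of its own, so no adjusted model can be written until one measure is chosen.

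**B2.5 may not ignore baseline.** A reader might infer an end-score-only comparison, because B2.7 speaks of change and B2.5 does not. The document does not say so, and it lists a baseline assessment for this outcome. What can be said is that the row names a comparison of group mean scores and leaves the use of baseline open. The end-score figures apply only if that reading is right.

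**Change scores use the baseline, and randomization protects against bias.** Both are true. It would be wrong to say that the baseline data are thrown away or that the comparisons are biased on average. The loss is in precision and in sensitivity to the imbalance that happens to occur.

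**Table cells are short labels, and adjustment may be in an analysis plan that is not shown.** This stands only in part. Such a plan could add covariates, but Table 2 states a method for each outcome, and a stated method can be improved.

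**It is a pilot.** The sample size was set for feasibility, no test or power is stated for clinical outcomes, and Impact of research leaves clinical outcomes as primary to the definitive trial. This limits the consequence but does not remove it.

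**Conclusion.** The point holds in a limited form. Table 2 names unadjusted comparisons for outcomes that also have a baseline measurement, and baseline-adjusted analysis would be more precise for EQ-5D-5L, MedQOL and medication knowledge. The gain over change scores is 15% to 35% of variance across the assumed r of 0.3 to 0.7. Because standard errors scale with the square root, that is about 8% to 19% narrower intervals (√0.85 = 0.92, √0.65 = 0.81). If B2.5 is an end-score comparison, its variance gain is 9% to 51%. These figures rest on equal SDs and an assumed r.

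For B1.1 the first defect is that three descriptions of one outcome disagree. Adjustment is worthwhile for a count or score change and pointless for the percentage.

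A reader might go further and conclude that the primary clinical comparison is biased or invalid. The documents do not support that: allocation is randomized, and recruitment, retention and cost criteria are unaffected. The change is worth making because it costs almost nothing.

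**What to change.** 1. **B2.7 and B2.5:** replace the Table 2 entries with a linear model of the 3-month score on arm and that patient's baseline score, fitted separately for EQ-5D-5L, MedQOL and medication knowledge. Report the adjusted mean difference with a 95% CI.
2. **B1.1:** state one measure and use it in both columns of Table 2 and in Primary outcomes. If it is a count or a score change, adjust for the baseline problem count or baseline score, for example by modelling the end-of-study problem count on arm and baseline count. If the percentage is kept, name it as the quantity compared and remove the reference to score changes. Adjustment for baseline count is then unnecessary.

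The cost is a wording change in Table 2 and Primary outcomes, and one degree of freedom per adjusted model. No new data, visits or patients are needed, and the planned total of 60 is unchanged. The choice should be recorded before the blinded data are analysed.
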